## Abstract

**Introduction:**

Acupuncture is an efficacious and safe treatment choice for migraine prevention. Results from clinical trials have shown that non-specific effects play an important role in acupuncture's efficacy. To date, however, there is no evidence available quantitatively evaluating the effect of non-specific effects, such as patients' expectations and beliefs for acupuncturists, on acupuncture efficacy, necessitating further exploration.

**Methods:**

A total of 156 patients with migraine without aura (MwoA) will be randomized to either junior or senior acupuncturist group, at a ratio of 1:1. The study will last 24 weeks, for each patient, comprising baseline, treatment, and follow-up phases lasting 4, 8, and 12 weeks, respectively. All patients will undergo 12 sections of acupuncture treatment delivered by either a junior or senior acupuncturist following the same acupuncture prescription and manipulation. The primary outcomes will be changes in the number of migraine days and frequency of attacks per 4 weeks cycle, relative to the baseline. Secondary outcomes will include severity of headache pain, quality of life, anxiety/depression levels, and use of non-steroidal anti-inflammatory drugs (NSAIDs) per 4 weeks cycle, compared to the baseline, as well as adverse events and rate of positive response to treatment. Prior to randomization of patients into junior or senior acupuncturist groups, the Acupuncture Expectations Evaluation Scale (AES) will be used to evaluate their expectations and belief with regards to acupuncture efficacy delivered by senior or junior acupuncturists.

**Discussion:**

Results from this clinical randomized controlled trial will help to quantitatively evaluate the extent of the effect of acupuncture treatment delivered by a senior or junior acupuncturist (high relative to low expectations) in migraine patients.

**Ethics and Dissemination:**

This trial has been approved by the Institutional Review Boards and Ethics Committees of Hospital of Chengdu University of Traditional Chinese Medicine (Approval No. 2020KL-058).

## Introduction

Migraine is a widespread neurological disorder that affects an estimated 1 billion people worldwide (1). Migraine has different subtypes, about 64% of which is migraine without aura (MwoA) subtype (2). According to the 2016 Global Burden of Disease Study, migraine is the second leading cause of disabilities, more than all other neurological disorders combined (3). Studies have estimated that in the UK alone, the direct and indirect costs associated with migraine are about £3.42 billion per year, taking into consideration disability, productivity loss, and healthcare costs (4). The current treatment therapies have not effectively managed migraine (3), necessitating exploration of additional effective, low-risk, and low-cost strategies.

Acupuncture, which is an important component of traditional Chinese medicine (TCM), has been used to treat headaches in East Asian countries for thousands of years. At present, it is also used for migraine treatment across many other regions worldwide, owing to its significant efficacy, few side effects, and cost-effectiveness (5–7). Results from numerous clinical trials have confirmed the immediate and long-term effects of acupuncture on migraine headaches and their corresponding symptoms, such as number of migraine days, headache frequency, and headache intensity (8–12). Although acupuncture is an effective and safe therapy for treatment of migraine, a recent report from Cochrane Database of Systematic Reviews revealed that non-specific effects play an important role in its efficacy (13). To date, however, little is known regarding to what extent the effects of acupuncture for migraine are mediated by context variables, such as patients' expectations of the acupuncturist, their preference for treatment choices, and culture background, among others. Therefore, further explorations are needed to elucidate the extent to which these factors affect acupuncture-based treatment of migraine.

In China, there is a popular proverb that says, “old TCM physician,” meaning that old- and high-level TCM physicians are more experienced. Therefore, patients prefer to consult senior and high-level TCM physicians for acupuncture treatment, because they believe that more experienced and high-level acupuncturists will bring them better therapeutic efficacy. However, in some cases, both senior and junior acupuncturists follow similar and standard acupuncture prescription and manipulation. Patients' expectation for the acupuncturist might influence the clinical efficacy. However, up to now, there is no evidence available quantitatively evaluating the extent of the effect of patients' expectation and confidence of an acupuncturist in acupuncture treatment for migraine.

Based on the above, in this study, we hypothesize that patients' expectation and confidence of an acupuncturist might have a potential impact on acupuncture efficacy. Therefore, this randomized controlled trial (RCT) aims to quantitatively evaluate the extent of the effect of acupuncture treatment delivered by either a senior (high expectation) or junior (low expectation) acupuncturist during treatment of migraine patients.

## Methods and Analysis

### Objective

To quantitatively evaluate the extent of the effect of acupuncture treatment delivered by either a senior (high expectation) or junior (low expectation) acupuncturist in migraine patients.

### Hypotheses

(1). Patients have higher expectations of a senior than a junior acupuncturist.(2). Patients treated by a senior acupuncturist group exhibit moderately better therapeutic effect after acupuncture treatment than those in the junior acupuncturist group.

### Study Design

This will be a single-center, two parallel-group, randomized clinical trial. A total of 156 MwoA patients will be recruited, then randomly allocated to either senior or junior acupuncturist groups, at a ratio of 1:1. The study will be conducted for a period of 24 weeks for each patient, comprising the following phases: baseline (4 weeks), treatment (8 weeks), and follow-up (12 weeks). AES will be used to evaluate patients' expectations for acupuncture efficacy delivered by either a junior or senior acupuncturist before randomization. A summary of the study protocol is presented using a flowchart (Figure 1) while the schedule is outlined in Table 1. This protocol is reported in accordance with the guidelines of the Consolidated Standards of Reporting Trials (CONSORT) (14) and Standards for Reporting Interventions in Clinical Trials of Acupuncture (STRICTA) (15).

**Figure 1 F1:**
[figure not shown]
Study flowchart.

**Table 1 T1:** Standard Protocol Items: Recommendations for Interventional Trials (SPIRIT) schedule of the trial.

	**STUDY PERIOD**								
	**Baseline**			**Treatment**			**Follow-up**		
**TIMEPOINT**	**-4-week**	**0-week**	**2-week**	**4-week**	**6-week**	**8-week**	**12-week**	**16-week**	**20-week**
**ENROLLMENT:**									
Eligibility screen	**×**								
Informed consent		**×**							
**INTERVENTION:**									
Senior acupuncturist acupuncture treatment									
Junior acupuncturist acupuncture treatment									
**ASSESSMENTS:**									
The headache diary									
Number of days with migraine	**×**	**×**		**×**		**×**	**×**	**×**	**×**
Frequency of migraine attacks	**×**	**×**		**×**		**×**	**×**	**×**	**×**
Positive response rate				**×**		**×**	**×**	**×**	**×**
Mean VAS score		**×**		**×**		**×**	**×**	**×**	**×**
SAS score		**×**		**×**		**×**	**×**	**×**	**×**
SDS score		**×**		**×**		**×**	**×**	**×**	**×**
The use of NSAIDs									
MIDAS		**×**		**×**		**×**	**×**	**×**	**×**
MSQ		**×**		**×**		**×**	**×**	**×**	**×**
AES		**×**							
MASS									
**PARTICIPANTS SAFETY:**									
Laboratory test		**×**				**×**			
Adverse events									

*This study includes 4-week baseline period, 8-week treatment period and 12-week follow-up period for each migraine patient*.

*AES, acupuncture expectations evaluation scale; MASS, Massachusetts General Hospital acupuncture sensation scale; MIDAS, Migraine Disability Assessment Scale; MSQ, Migraine-Specific Quality-of-Life Questionnaire; NSAIDs, nonsteroidal anti-inflammatory drugs; SAS, self-rating anxiety scale; SDS, self-rating depression scale; VAS, visual analog scale; Laboratory test: including routine examination of blood, urine and stool, blood biochemical test (including liver and kidney function), and electrocardiogram examination*.

### Patient Recruitment

Potential MwoA patients are currently being recruited from outpatient clinics at the Hospital of Chengdu University of Traditional Chinese Medicine, local communities, and WeChat advertisements. The recruitment time started in March 2021 and will end in December 2023.

### Eligibility Criteria

All potential MwoA patients will be assessed face-to-face for eligibility by neurologists of Hospital of Chengdu University of Traditional Chinese Medicine according to the following inclusion and exclusion criteria.

#### Inclusion Criteria

Participants will be recruited if they:

(1) are aged between 18 to 65 years;(2) are diagnosed with MwoA according to the international classification of headache disorders (ICHD-3) 2018 (16);(3) have a history of MwoA for over 6 months;(4) have had MwoA attacks, 2–8 times per month in the past 3 months. These attacks should have lasted 4–72 h without or at least 2 h with medication;(5) voluntarily sign an informed consent.

#### Exclusion Criteria

Participants will be excluded if they:

(1) are accompanied with any other chronic pain conditions or have a history of head trauma (with loss of consciousness) or mental retardation;(2) are suffering from psychiatric, respiratory, cardiovascular, or renal illnesses;(3) have previously received acupuncture treatment, or taken any prophylactic headache medicine in the last 1 month;(4) have a history of alcohol and/or other substance abuse or dependence;(5) are carrying a pregnancy, ready to be pregnant, or lactating mothers;(6) have acupuncture contraindications, such as bleeding tendency;(7) are unable to cooperate with acupuncture treatments;(8) are participating in other trials within 3 months before recruitment.

### Randomization and Allocation Concealment

Patients will be randomly assigned to either group A or B, using a computerized randomization sequence form according to the random number table method. Odd and even numbers will be allocated to the senior (group A) and junior (group B) acupuncturist groups, respectively. Sealed opaque envelopes, with patients screening sequence numbers and group names printed on the outside and inside, respectively, will be used for the allocation. All the recruited patients will be numbered consecutively and connected correspondingly to the envelopes. After the baseline observation phase, the envelopes will be opened, and patients will be randomly assigned to either of the two groups.

### Blinding

Patients and acupuncturists will not be blinded due to the design and purpose of this study. Data collectors, outcome assessors, and data analysts will be blinded to the allocation.

### Sample Size Estimation

There is no available reference of clinical trials regarding the effect of patients' expectations of different acupuncturists on acupuncture-based migraine treatment so far. Our clinical experience and results from preliminary experiments indicate that the reduction number of migraine days was 3.9 ± 2.49 in the senior acupuncturist group, compared to 2.7 ± 3.45 days in the junior acupuncturist group at weeks 4–8 of treatment. PASS software version 15 was used to calculate the sample size, based on 80% power to detect a significant difference (α = 0.05, two sided), and with an excepted dropout rate of ~20%, target enrollment was set at 156 patients (78 patients in each group).

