### Limitations

We anticipate a few limitations in the study. Firstly, although the evaluator, outcome assessor, and data analyst will be blinded, it is impossible to blind the acupuncturist due to the nature of treatment. Secondly, different acupuncturists may not achieve completely uniform acupuncture, thus both the senior and junior acupuncturist will be trained to strictly to follow the same acupuncture procedure in an attempt to minimize differences in efficacy. In addition, it is not excluded that our preliminary experimental results may underestimate the sample size and lead to false negative results.

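### The stated assumptions need about 100 evaluable and 125 enrolled patients per arm for 80% power; the planned 78 per arm gives about 60%, and at most about 70%.

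*Protocol article*

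**What the plan says.** The Sample Size Estimation section of the protocol article gives every input needed to repeat the calculation. From clinical experience and preliminary experiments, "the reduction number of migraine days was 3.9 ± 2.49 in the senior acupuncturist group, compared to 2.7 ± 3.45 days"; the second figure is for the junior arm, and the period is given as weeks 4 to 8. The calculation is described as "based on 80% power to detect a significant difference", with the significance level given as "α = 0.05, two sided". The result is stated as: "with an excepted dropout rate of ~20%, target enrollment was set at 156 patients (78 patients in each group"). Allocation is 1:1 (Study Design). The Statistical Analysis section plans two-tailed tests at the 5% level, with a Student's t-test for normally distributed data and a nonparametric test otherwise. The Limitations section adds that "it is not excluded that our preliminary experimental results may underestimate the sample size and lead to false negative results".

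**The concern.** The figure of 78 per arm is presented as already including a 20% dropout allowance, so about 62 evaluable patients per arm should be enough for 80% power. The assumed difference is 1.2 days against a typical SD of about 3.0 days, a standardised difference of about 0.40. At two-sided 5% that needs roughly 100 per arm, not 62.

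The trial sets out to quantify how much the choice of acupuncturist matters. The section on implications for clinical practice raises, in hedged terms, the possibility that senior and junior acupuncturists achieve similar efficacy, and it expects the findings to guide practice. A reader who trusts the stated 80% would give a non-significant result more weight than the design supports.

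**Working it through.** **Inputs** (Sample Size Estimation, unless noted)
- Difference: 3.9 − 2.7 = 1.2 days
- Variances: 2.49² + 3.45² = 6.20 + 11.90 = 18.10; root-mean-square SD = √(18.10/2) = 3.009; standardised difference 1.2/3.009 = 0.399
- Two-sided α = 0.05 (z = 1.960); power 80% (z = 0.842); dropout 20%
- Allocation 1:1 (Study Design)

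**Required size from these inputs**

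n per arm = (z_α + z_β)² × (SD₁² + SD₂²) / Δ² = (1.960 + 0.842)² × 18.10 / 1.2² = 7.849 × 18.10 / 1.44 = 98.7, so 99.

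With the noncentral t distribution (Welch), power is 79.7% at 99 and 80.1% at 100, so 100 per arm. Dropout: 99/0.8 gives 124 and 100/0.8 = 125 per arm, or 248 to 250 in total. Multiplying by 1.2 instead of dividing by 0.8 still gives 119 to 120 per arm.

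**Attempts to reproduce 78 per arm at two-sided 5% and 80% power**

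| SD used | Evaluable per arm (normal / t) | Enrolled per arm, ÷ 0.8 | Enrolled per arm, × 1.2 |
|---|---|---|---|
| As stated | 99 / 100 | 124 / 125 | 119 / 120 |
| 2.49 in both arms | 68 / 69 | 85 / 87 | 82 / 83 |
| Average of the two SDs | 97 / 98 | 122 / 123 | 117 / 118 |
| 3.45 in both arms | 130 / 131 | 163 / 164 | 156 / 158 |

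No row gives 78 per arm, before or after dropout. Even the smaller SD in both arms exceeds 78 once dropout is allowed for.

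Two routes do arrive at the stated numbers, and both depart from the stated method:
- One-sided 5% with no dropout allowance: (1.645 + 0.842)² × 18.10 / 1.44 = 77.7, so 78 per arm (79 by the t-test).
- SD 3.45 in both arms, with the per-arm 130 taken as the trial total: 130 × 1.2 = 156.

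The document does not show which slip, if either, occurred.

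**Power of the planned enrolment for 1.2 days (two-sided 5%)**

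| Evaluable per arm | Normal approximation | t-test (Welch) |
|---|---|---|
| 62 (78 × 0.8 = 62.4) | 60.3% | 59.5% |
| 78 (no dropout) | 70.2% | 69.6% |
| 100 | 80.5% | 80.1% |

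**Detectable difference and precision**
- 62 per arm: SE = √(18.10/62) = 0.540; detectable with 80% power = 2.802 × 0.540 = 1.51 days; expected 95% CI half-width about 1.07 days
- 78 per arm: SE = √(18.10/78) = 0.482; detectable = 2.802 × 0.482 = 1.35 days

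**The case against.** - **The Limitations section already warns of false negatives.** It does, but the warning concerns whether the preliminary results can be relied on. The mismatch here remains if those results are exactly right, and the 80% is still stated without qualification.
- **60% assumes the full 20% is lost and contributes nothing.** This is fair. Intention-to-treat analysis is planned where possible, and 20% is only an expected rate. The honest range is about 60% to 70%. The lower end uses the plan's own dropout assumption, and the upper end still misses 80%.
- **The origin of 78 is unknown.** This also stands. Two different slips lead to the stated numbers, so neither should be presented as the cause. The finding does not depend on it.
- **Covariate adjustment could reduce the requirement.** To manage with 62 per arm, the covariates would need a correlation with the outcome of about √(1 − 62/98.67) = 0.61. The document states no such figure, and the group comparison it describes is a t-test.
- **The text on similar efficacy is speculative and sets no decision rule.** Correct. The risk lies in how a null result would be read; the protocol does not commit itself to that reading.
- **1.2 days is not described as a minimal important difference.** Also correct. A rule for interpreting the confidence interval against 1.2 days is advice on reporting and goes beyond correcting the arithmetic.

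**Conclusion.** The concern holds. On the document's own assumptions, 156 patients do not give 80% power for the planned 1.2-day difference. Power is about 60% with the planned 20% dropout and about 70% with none, so the chance of missing the planned effect is 1.5 to 2 times the stated 20%. Meeting the stated target would take about 250 enrolled, roughly 60% more than planned (250/156 = 1.60). This rests on the quoted means and SDs, 1:1 allocation, a two-sided 5% t-test, and patients lost to follow-up contributing nothing in the 62-per-arm case. The stated power should be corrected, because it is a central design property and is wrong by 10 to 20 percentage points.

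**What to change.** Rewrite the Sample Size Estimation paragraph so that the number, power and assumptions agree. Suggested content: with the quoted means and SDs and a two-sided 5% t-test, 80% power for a 1.2-day difference would need 100 evaluable and 125 enrolled patients per arm; the planned 156 patients (about 62 evaluable per arm after 20% dropout) give about 60% power for 1.2 days (about 70% with no dropout), or 80% power for a difference of about 1.5 days. In Limitations, separate this known shortfall from the uncertainty in the preliminary results.

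It would also help to say in the Discussion that a non-significant result does not show similar efficacy, and that it should be read from the 95% confidence interval, including whether the interval excludes the 1.2 days used for planning.

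The cost is wording only: a stated figure becomes less favourable, with no extra patients and no change to conduct. If the sponsor wants to keep 80% power for 1.2 days, the alternative is to raise the target to about 250, at the cost of 94 more patients (250 − 156) and any recruitment time they require.

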### Intervention

All MwoA patients will undergo acupuncture treatment, delivered by either a senior or junior acupuncturist, following the same protocol of acupuncture prescription and manipulation. The acupuncture prescription will follow the guidelines of whole head headache treatment, described in the national textbook of Chinese Acupuncture and Moxibustion for TCM students in mainland China. This includes Baihui (GV20), bilateral Touwei (ST8), bilateral Shuaigu (GB8), bilateral Taiyang (EX-HN5), bilateral Fengchi (GB20), bilateral Hegu (LI4), and bilateral Taichong (LR3).

The acupuncture procedure will be as follows: local skin disinfection will first be performed, then acupuncture needles, with a diameter of 0.25 mm, and a length of 40 or 15 mm (Hwatuo, Suzhou, China), inserted perpendicularly, subcutaneously, or obliquely into the acupoints. After provocation of deqi (needle sensation) (17), the needles will be maintained therein for 60 min, with manipulation once every 20 min during this period, to maintain deqi sensation. Each MwoA patient will undergo 12 sessions of acupuncture treatment, lasting a period of 8 weeks. The treatment will be performed twice a week, for the first 4 weeks, and once a week for the next 4 weeks. All the acupuncture treatments in senior acupuncturist group will be delivered by a licensed senior acupuncturist with an associate professor title. On the other hand, procedures in the junior acupuncturist group will be delivered by a licensed junior acupuncturist with an intern title. Prior to commencement of the study, both acupuncturists were trained to follow the same acupuncture procedure to minimize differences in acupuncture manipulation parameters. See Table 2 and Figure 2 for details of the location and manipulation of the acupoints.

**Table 2 T2:** Details of the acupoints location and insertion.

**Acupoints**	**Location**	**Depth of insertion**
*Baihui* (GV20)	On the head, 5 cun superior to the anterior hairline, on the anterior median line	0.5–0.8 cun (12.5–20 mm) subcutaneous insertion.
*Shuaigu* (GB8)	On the bilateral head, directly superior to the auricular apex, 1.5 cun superior to the temporal hairline.	0.5–0.8 cun (12.5–20 mm) subcutaneous insertion.
*Fengchi* (GB20)	In the anterior region of the neck, inferior to the occipital bone, in the depression between the origins of sternocleidomastoid and the trapezius muscles.	0.5–0.8 cun (12.5–20 mm) oblique insertion toward the tip of the nose.
*Touwei* (ST8)	On the bilateral head, 0.5 cun directly superior to the anterior hairline at the corner of the forehead, 4.5 cun lateral to the anterior median line.	0.5–0.8 cun (12.5–20 mm) subcutaneous insertion.
*Taiyang* (EX-HN5)	At the bilateral temporal part of the head, in the depression 1 cun posterior of the midpoint of the ligature between lateral end of the eyebrow and the outer canthus.	0.3–0.5 cun (7.5–12.5 mm) perpendicular insertion.
*Hegu* (LI4)	On the dorsum of the hand, radial to the midpoint of the second metacarpal bone.	0.5–0.8 cun (12.5–20 mm) perpendicular insertion.
*Taichong* (LR3)	On the dorsum of the foot, between the first and second metatarsal bones, in the depression distal to the junction of the bases of the two bones, over the dorsalis pedis artery.	0.5–0.8 cun (12.5–20 mm) perpendicular insertion.

*The name, English code and location of each acupoint is in accordance with WHO Standard Acupuncture Point Locations in the Western Pacific Region. Retaining needles for 60 mins. Lifting, thrusting, twisting and/or rotating the needles once every 20 mins with intermittent stimulation for maintaining the deqi sensation for twice. Cun belongs to proportional measurement unit for acupoints locating. EX-HN, Extrachannel points; GB, Gallbladder Meridian; GV, Governor Vessel; LI, Large Intestine Meridian; LR, Liver Meridian; ST, Stomach Meridian*.

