#### Evaluation of Patient's Expectations

The patient's expectation will be measured by AES (Appendix 1), including the expectation of the acupuncturist and the expectation of acupuncture therapy. Each patient will be asked to rate their expectation and confidence level for a junior and senior acupuncturist, respectively, using two opposing questions before randomization. The questions are as follows: “How much confidence do you have in senior acupuncturists to relieve your migraine symptoms?” and “How much confidence do you have in junior acupuncturists to relieve your migraine symptoms?” Each question adopts the percentile system, which is scored as summary percentile scales ranging from 0 to 100. Higher scores imply greater expectation and confidence. Besides, the other item of AES will be used to evaluate the patient's expectation of acupuncture therapy as a covariate.

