### Strict Quality Control Details to Help us Better Achieve Our Aim

In order to achieve our aim and have the results more reliable and replicable, we made several strict quality control details to control the quality of this trial. The details are as follows. (1) We will control the gender of the acupuncturist (both male) to exclude any potential influence of the operator's gender on the patients' expectation. (2) Acupuncturists will not be present during evaluation of clinical outcomes, to prevent excessive evaluation bias. (3) Acupuncturists have been adequately trained, and will be expected to follow the same acupuncture procedures, including acupuncture prescription, needle angle, direction, manipulation, and stimulation, among others. (4) To prevent the risk bias on the results, data collectors, outcome assessors, and data analysts will be blinded to the allocation. (5) In order to ensure compliance by all researchers, group meetings will be held every week for communication and study, and solutions will be put forward in time if difficulties or problems are encountered in the trial.

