### Potential Implication of Trial Findings for Future Clinical Practice

In clinical practice, identification of practitioners who are sufficiently qualified to deliver acupuncture treatment is imperative in accurate decision making. Patients' expectations of acupuncturists or acupuncture treatment, and acupuncturists' TCM diagnosis and treatment capability, might be the key components determining who might be qualified enough to deliver acupuncture. However, these components are often mixed. Results from this trial will quantitatively clarify whether or not patients' expectations of different acupuncturists do influence acupuncture efficacy in treatment of migraine. It is possible that all the licensed acupuncturists, whether high-level or interns, might deliver similar acupuncture efficacy in migraine patients if they follow the appropriate acupuncture procedures. If this is not the case, the findings of this trial are expected to ascertain to what extent this effect size might be. We envisage that our findings will guide future acupuncture clinical trials and acupuncture clinical practice.

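### One practitioner treats each arm, so the senior-junior difference cannot be read as the effect of patients' expectations or as a general effect of seniority

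*Protocol article*

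**What the plan says.** All of the following is in the protocol article.

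- **Who treats.** Intervention: "All the acupuncture treatments in senior acupuncturist group will be delivered by a licensed senior acupuncturist with an associate professor title", and "procedures in the junior acupuncturist group will be delivered by a licensed junior acupuncturist with an intern title". The same section adds that "both acupuncturists were trained to follow the same acupuncture procedure to minimize differences in acupuncture manipulation parameters". The quality-control part of the Discussion says: "We will control the gender of the acupuncturist (both male) to exclude any potential influence of the operator's gender on the patients' expectation". Limitations also speaks of one senior and one junior. The total is two practitioners.
- **What the arms stand for.** The Introduction, the Objective and the Discussion paragraph of the Abstract label the senior arm high expectation and the junior arm low expectation. The main Discussion presents the trial as the first randomised trial to quantify the effect of expectations of an acupuncturist.
- **What is promised.** Potential Implication of Trial Findings for Future Clinical Practice: "Results from this trial will quantitatively clarify whether or not patients' expectations of different acupuncturists do influence acupuncture efficacy in treatment of migraine".
- **What is measured.** Evaluation of Patient's Expectations: "Each patient will be asked to rate their expectation and confidence level for a junior and senior acupuncturist, respectively". These ratings (the Acupuncture Expectations Evaluation Scale, AES) run from 0 to 100 and are taken before randomisation. They serve the first hypothesis, "Patients have higher expectations of a senior than a junior acupuncturist". Only the separate item on acupuncture therapy is named as a covariate.
- **What is analysed.** Statistical Analysis names two-group tests. Needle Sensation Evaluations adds the needle-sensation scale (MASS) as a covariate.

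**The concern.** The trial sets out to isolate expectation, but the randomised contrast is between two people. Those people differ in rank, which is meant to drive expectation, and also in experience, communication and everything else that distinguishes one clinician from another. If the senior arm does better, the text as written would credit expectation and extend the result to seniors and juniors at large. The difference could come wholly or partly from the two individuals. The stated analysis has no means of noticing this, because with one practitioner per arm the variation between practitioners cannot be estimated.

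**Working it through.** **Structure.** This part needs no figures.

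1. Practitioners per arm: 1. Knowing the arm is knowing the practitioner, so a model cannot hold both an arm effect and a practitioner effect.
2. Within an arm there are 1 − 1 = 0 degrees of freedom for variation between practitioners.
3. Arm difference = expectation effect + difference in all other traits of the two people. There is one equation and two unknowns.

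The safeguards against this:

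| Safeguard | What it covers | What it leaves |
|---|---|---|
| Common training | Prescription and needling technique | Skill in execution, manner, communication; Limitations concedes delivery may not be uniform |
| Both male | Gender | Every other personal trait |
| MASS as covariate | Needle sensation | Everything else; it is recorded after each session, so after randomisation, and may itself respond to expectation |
| Therapy item of the AES as covariate | Expectation of acupuncture as such | Expectation of the practitioner, and practitioner traits |

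**Illustration for a general senior-versus-junior claim.** The plan gives no figure on this point to reproduce. Inputs from Sample Size Estimation: SDs 2.49 and 3.45, planned difference 3.9 − 2.7 = 1.2 days, 78 per arm, about 20% dropout. Completers: 78 × 0.8 = 62.4, taken as 62. The practitioner ICC is not in the document; 0.01, 0.02 and 0.05 are assumed. The stated SDs are taken as SDs among patients of one practitioner.

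- Average SD = √((2.49² + 3.45²)/2) = √((6.2001 + 11.9025)/2) = 3.009.
- Patient-level standard error = 3.009 × √(2/62) = 0.540 days.
- Practitioner component of the standard error = 3.009 × √(2 × ICC/(1 − ICC)).
- Inflation factor R = √(1 + 62 × ICC/(1 − ICC)).
- False-positive rate of the nominal 5% test = 2 × (1 − Φ(1.96/R)).

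| Assumed ICC | Practitioner component (days) | R | True standard error (days) | False-positive rate |
|---|---|---|---|---|
| 0 | 0 | 1 | 0.540 | 5.0% |
| 0.01 | 0.43 | 1.275 | 0.689 | 12.4% |
| 0.02 | 0.61 | 1.505 | 0.813 | 19.3% |
| 0.05 | 0.98 | 2.065 | 1.116 | 34.2% |

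The practitioner component does not contain the number of patients, so recruiting more does not shrink it. With 78 per arm in place of 62, the false-positive rates are 14.3%, 22.3% and 38.6%. They rise because the patient-level error falls while the practitioner component stays. At an ICC of 0.05, the chance difference between two practitioners has an SD of 0.98 days, against a planned difference of 1.2 days.

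**The case against.** The best reply has four parts.

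- **The randomised comparison is valid.** This stands, for the question it answers: whether patients fare differently with this senior than with this junior. The core wording of the Objective, read without its bracketed labels, is close to that question.
- **The authors took precautions and state a limitation.** This stands as mitigation. None of it separates expectation from the person, and Limitations mentions non-uniform delivery without drawing the consequence for the conclusion.
- **A condensed article leaves analyses to a fuller plan.** This stands for analysis detail. A reader might infer that the lack of a paired test for the first hypothesis is a defect. It is routine detail that an article may omit, and nothing says the paired ratings will go unanalysed. However, no analysis plan can undo one practitioner per arm.
- **The error rates rest on assumed ICCs.** They do. They also concern generalisation to other practitioners and do not measure how much of a difference is expectation.

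Three stronger readings are tempting and not supported:

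- A reader might infer that the article admits its own confounding where it says that expectation and practitioner capability are often mixed. That sentence describes clinical practice, not this trial.
- A reader might infer that the trial's confidence intervals will be too narrow. The article mentions none.
- A reader might infer that the paired ratings would settle the matter. They cannot: the ratings are not randomised, and Appendix 1 asks about senior and junior acupuncturists in general, not these two.

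**Conclusion.** The point holds as a limit on what may be concluded. With one practitioner per arm, the contrast is fully aliased with the traits of two individuals. It supports neither the claim to quantify the effect of expectations nor a general statement about seniors and juniors. This follows from the staffing of the arms alone and rests on no assumed number. For the general claim, the false-positive rate of a nominal 5% test would be about 12%, 19% or 34% at assumed ICCs of 0.01, 0.02 or 0.05 with 62 per arm. These figures illustrate scale and are not estimates for this trial. The comparison between the two named roles as staffed here remains sound.

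**What to change.** 1. **Wording.** Restate the objective and the intended conclusion as a comparison of treatment by this senior with treatment by this junior practitioner. Remove the statements that the arm difference measures the effect of expectation (Abstract, Introduction, Objective, Discussion and the section on implications). Name the one-practitioner design under Limitations.

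2. **Supportive analysis.** Before unblinding, specify a model of outcome on baseline value, arm, AES gap (senior minus junior rating) and arm × gap. The arm effect at gap g is then the arm coefficient plus g times the interaction coefficient. If expectation drives the difference, the senior advantage should grow with the gap and be near zero at gap 0. A fixed advantage of one person over the other would remain at gap 0. State with the model that:
   - the gap is not randomised;
   - the items concern acupuncturists in general;
   - few patients may lie near gap 0, since the first hypothesis predicts positive gaps;
   - power for the interaction is limited.

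The ratings are already collected before randomisation, so no new data and no change to treatment are needed, although recruitment has begun. The cost is a narrower conclusion and one extra low-power model, to be labelled supportive.
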